## Abstract

**Background:**

Home noninvasive positive pressure ventilation (NIPPV) has become evidence-based care for stable hypercapnic chronic obstructive pulmonary disease (COPD) patients. There are still other challenges including appropriate follow-up, telemonitor, and management to ensure treatment effectiveness, compliance, and security and to improve quality of life. The Internet of things (IOT) is the name given to the network of devices and other “things” with built-in sensors, software, electronics, and network connectivity, communicating these objects over wireless networks and sending data to a cloud platform. The study aims to evaluate the effectiveness and safety of the IOT-based management of NIPPV for the COPD patients with hypercapnic chronic respiratory failure.

**Methods:**

This multicenter, prospective, randomized controlled trial was conducted with a total of 200 COPD patients with chronic hypercapnic respiratory failure. Using a computer-generated randomization process, patients were randomized (in a 1:1 ratio) into the usual NIPPV (control group) or to receive additional IOT-based management (intervention group) for 12 months. The primary outcome was the Severe Respiratory Insufficiency (SRI) questionnaire. Secondary outcomes included compliance with the ventilator, gas exchange, lung function, health-related quality of life, hospitalization frequency, time to death within 1-year, all-cause mortality, safety analysis, and cost-effectiveness analysis.

**Discussion:**

This study will be the first and largest randomized trial in China to evaluate the effectiveness and safety of the IOT-based management of NIPPV for COPD patients with chronic hypercapnic respiratory failure. The results will help to understand the current situation of IOT-based home ventilation and may provide new evidence for home NIPPV treatment and management in the future.

**Trial registration:**

Chinese Clinical Trials Registry ChiCTR1800019536. Registered on 17 November 2018.

**Supplementary Information:**

The online version contains supplementary material available at 10.1186/s13063-022-06372-z.

## Background

Home non-invasive positive pressure ventilation (NIPPV) has long been undetermined in patients with stable chronic obstructive pulmonary disease (COPD) with chronic hypercapnic respiratory failure (CHRF) [1–7]. Previous research yielded conflicting results on survival, re-hospitalization, lung function, gas exchange, exercise tolerance, and quality of life [3–8]. However, recent randomized controlled trials have indicated that high-intensity NIPPV, which used high levels of inspiratory positive airway pressure (IPAP) with a high backup respiratory rate aimed at maximal PaCO2 reduction, showed physiological and clinical benefits [9, 10]. On the basis of these positive results, a recent meta-analysis demonstrated that home NIPPV was associated with a lower risk of mortality and all-cause re-hospitalization compared with no device support, but no significant difference in quality of life had been identified [11]. NIPPV has become evidence-based care for stable hypercapnic COPD patients [12–14].

There are still other challenges including appropriate follow-up, telemonitor, and management to ensure treatment effectiveness, adherence, and security and to improve quality of life. Usually, hospitals prescribe NIPPV, companies sold the ventilator while patients have little information of knowing how to use and maintain NIPPV at home [15, 16]. In fact, actively monitoring, communicating information, and solving problems during follow-up were crucial for long-term adherence and clinical outcomes [1, 16–18]. Furthermore, home NIPPV can be considered not only as a treatment, but also as a tele-monitoring predictor of objectively detecting acute exacerbations of COPD onset [16, 18]. However, the increasing number and costs of ventilator-dependent individuals make health providers largely insufficient to face the demands.

The Internet of things (IOT) is the name given to the network of devices and other “things” with built-in sensors, software, electronics, and network connectivity, communicating these objects over wireless networks and sending data to a cloud platform [19, 20]. The IOT medical technology would inform not only physicians but patients of real-time data to identify and early prevent issues [20–23]. Nowadays, many ventilatory devices are embedded with electronics, software, sensors, and network connectivity, which collect, provide and exchange information about compliance, ventilatory parameters, and physiological indices. With more reliable tele-monitoring and transmission technology, IOT-based management of continuous positive airway pressure (CPAP) in obstructive sleep apnea syndrome (OSA) patients, such as follow-up and tele-monitoring on adherence with the use of IOT, is emerging and yielding some positive findings [24–26]. Duiverman et al. [27] conducted the first RCT about home initiation with the help of IOT of chronic NIPPV in COPD patients recently, which demonstrated that home titration was safe and non-inferior to in-hospital titration, and reduced costs by over 50% [27].

However, clear conclusions of IOT-based home NIPPV management in COPD patients with CHRF were lacking. The primary aim of this study was to evaluate the effectiveness (in terms of Health-related Quality of Life and compliance) and safety of the IOT-based management of NIPPV for the COPD patients with CHRF. The secondary aim was to determine whether IOT-based NIPPV is more cost-effective and non-inferior to standard management of NIPPV for decreasing PaCO2, risk of mortality, and all-cause hospital readmission.

## Methods

### Study design and patients

This trial was a multicenter, prospective, parallel-group, randomized controlled study recruiting 200 hypercapnia COPD patients with a 1:1 allocation to NIPPV alone or NIPPV plus IOT-based management. The protocol was written in compliance with the Standard Protocol Items: Recommendations for Interventional Trials guidelines (SPIRIT) and the complete SPIRIT checklist for the study is provided in Additional file 1.

The trial was approved by the Medical Ethics Committee of Zhongshan Hospital Fudan University, patients gave informed consent to participate in the study (Additional file 2) and the trial was registered on 17 November 2018 at the Chinese Clinical Trials Registry (ChiCTR1800019536). Patients were recruited from Zhongshan Hospital Fudan University, QingPu Branch of Zhongshan Hospital Affiliated to Fudan University, Xuhui District Central Hospital, The Central Hospital of Min-Hang District, Jiading District Central Hospital, Shanghai Pudong Hospital, Tongren Hospital Affiliated to Shanghai Jiaotong University, Liqun Hospital of Putuo District and followed up for 12 months. The approval of the protocol by other medical ethics committee at each participating center was obtained before recruitment was initiated. Patients were identified for eligibility when admitted to respiratory wards with an acute exacerbation of COPD and decompensated hypercapnic respiratory failure after resolution of the exacerbation and clinical stabilization.

The patients who meet all of the following inclusion criteria were considered eligible: (1) aged 40 to 80 years old; (2) clearly diagnosed patients with severe or very severe COPD (Global Initiative for Chronic Obstructive Lung Disease stage III or IV [1]): Forced Expiratory Volume in 1 s (FEV1)/forced vital capacity (FVC) < 70% and FEV1% < 50% predicted value after 400 mcg short-acting beta2-agonist (salbutamol); (3) combined with chronic respiratory failure (PaCO2 > 50 mmHg) during daytime in the steady state of COPD.

Patients were excluded if they (1) had unstable cardiac hemodynamics, such as acute left heart failure, unstable angina, and cardiogenic shock; (2) combined with typical pulmonary fibrosis, airway tumors, tuberculosis sequelae (lung damage), and other lung diseases; (3) combined with neuromuscular or chest wall disease.

### Randomization and masking

The randomization of the trial was completed at an independent data center (College of Public Health, Fudan University) using a computer-generated random number sequence with an allocation ratio of 1:1 for each group. All investigators at each of the participating hospitals contacted an independent statistician to obtain an identification code and a random number unique to this patient who fulfills the inclusion criteria. IOT-based management of NIPPV couldn’t be blinded, and an effective sham measure was not available. Supervising clinicians who performed NIPPV and IOT-based management were aware of the treatment assignment of every participant. The staff members conducting the outcome assessments and statistical analysts were blinded to treatment assignment.

### Intervention

In both groups, oxygen therapy (Airsep Oxygen Concentrator VisionAire 5L) was entrained into the NIPPV circuit and oxygen flow rate was initiated to control hypoxemia and hypoventilation aiming to maintain SpO2 > 88%. All patients were instructed to use oxygen therapy for at least 12 h daily. NIPPV was initiated by bi-level positive airway pressure (BiPAP) in the spontaneous/timed mode (Curative Lotus ST30) and adjusted the settings with the aim to: (1) maximally support respiration; (2) reduce at least 10 mmHg PaCO2 compared with the first night of spontaneous breathing or achieve normocapnia. We gradually increased the IPAP during trials to a maximal tolerated level aiming to tidal volume 8 ml/kg and to the maximal level that is tolerated by the patient. Expiratory positive airway pressure (EPAP) was started at 5 cmH2O. The respiratory rate was set as close as possible to the RR of the patient and the inspiration to expiration time was 1:3. All patients were initially given ventilation by means of a nasal, oral-nasal, or full-face mask according to patient preference and humidification to maximize comfort. They were advised to use NIPPV intermittently for at least 8 h per day, preferably continuous use during sleep, but usage during daytime was also accepted. The patient was discharged home once the gas exchange goals were achieved.

Patients in the control group received usual NIPPV management. Patients or their care providers underwent NIPPV training on NIPPV application and operation to enable support for home use of NIPPV prior to discharge. This included information on how to put on the mask, how to turn the device on and off, and the correct cleaning of the tubes, masks, and humidifier. When necessary, ventilator providers joined the patients at home to install the ventilator. Moreover, patients could contact the doctor by 24-h helpline in case of technical problems with the ventilator, or oxygen treatment.

In the intervention group, the optimized titration protocol of ventilator parameters in the hospital was the same as the control group. But patients would receive IOT-based management NIPPV therapy (Fig. 1). Medical management teams would establish a real-time monitoring IOT cloud platform (Suzhou Curative Medical Technology Limited Corporation) including clinical information, ventilator parameters, daily report, and follow-up information. Daily information was retrieved remotely via the 4th generation mobile communication technology (4G) system clicked on the back of the ventilator, which were sent to the secured platform including data collector, parse server, automatic processing server, data storage center, application interface server, and web server. This assessment of daily individual risk was associated with IOT tele-monitoring providing basic usage time, NIPPV pressures, mask leak, breaths per minute (BPM), tidal volume (VT), and residual respiratory events (Fig. 2). The IOT cloud platform allocated clinical information and daily report to medical staff members based on automatic processing of device data. The suggestions of risk intervention were also provided in the event of side effects, leaks, and lack of efficacy. Physicians were in charge of the complete integrated care management and appropriate adjustment of NIPPV treatment based on platform information and communication of patients. After the assessment of physicians, a specialized nurse practitioner would contact the patient, providing case-by-case problem-solving and specific interventions about how to minimize side effects and to improve compliance (interfaces changing, the addition of humidifiers, and so on). Arranged home visits were organized at 1, 4, and 8 months after the NIPPV was initiated, and patients were contacted by telephone every month. The nurse practitioner would provide user-friendly education programs, monitor health status, and ensure adherence to therapy at all home visits. Additionally, ventilator providers would detect problems with technical devices and do re-assessments of technical control of the equipment at all follow-up visits. Moreover, ventilator providers would replace consumable materials and provide 24-h helpline in case of technical problems with the ventilator or long-term oxygen treatment.

**Fig. 1 Fig1:**
[figure not shown]
IOT-based management of NIPPV

**Fig. 2 Fig2:**
[figure not shown]
The IOT cloud platform. BPM, breaths per minute; VT, tidal volume

General therapy for COPD, such as smoking cessation and pharmacologic therapy will be standardized according to the national treatment guidelines [28] in both groups during the study period. Pharmacological therapy will be guided by symptoms, risk of exacerbations, side effects, comorbidities, and the patient’s response.

### Follow-up and endpoints

The SPIRIT schedule for this trial was given in Table 1 and the study flow diagram was shown in Fig. 3. All eligible patients enrolled in the study underwent a baseline assessment of demographics, previous history, health-related quality of life, and measurement of chest CT, lung function, electrocardiogram, echocardiography, routine laboratory tests, and daytime gas exchange. All patients from both groups were admitted to the hospital for the follow-up visits to assess the measurements and ensure optimized medical treatment, including NIPPV. Regular follow-up visits were scheduled at 3, 6, and 12 months after the NIPPV was initiated. We provided a convenient follow-up process by setting a specialty advance appointment clinic.

**Table 1 Tab1:** SPIRIT schedule of enrollment, intervention, and assessments

Timepoint	Study period					
	**Enrolment**	**Allocation**	**Post-allocation**			**Close-out**
	**Day 0**	**Day 1**	***3 months***	***6 months***	***12 months***	***12 months***
**Enrolment:**						
** Eligibility screen**	X					
** Informed consent**	X					
** Allocation**		X				
**Interventions:**						
** NIPPV plus IOT**		X	X	X	X	
** NIPPV alone**		X	X	X	X	
**ASSESSMENTS:**						
** Demographics**	X					
** Comorbidity**	X					
** Vital signs**		X	X	X	X	
** Hospital readmission**		X	X	X	X	
** Exacerbation**		X	X	X	X	
** Survival status**		X	X	X	X	
** Arterial blood gases**		X	X	X	X	
** Lung function**		X			X	
** SRI score**		X	X	X	X	
** CAT score**		X	X	X	X	
** mMRC score**		X	X	X	X	
** cNAT score**		X	X	X	X	
** Compliance**		X	X	X	X	
** Chest CT**		X			X	
** Electrocardiogram**		X			X	
** Echocardiography**		X			X	
** Routine laboratory tests**		X			X	
** Cost-effectiveness**		X	X	X	X	
** Safety**		X	X	X	X	

*NIPPV* noninvasive positive pressure ventilation, *IOT* Internet of things, *SRI* severe respiratory insufficiency questionnaire, *MRC* Medical Research Council score, *CAT* COPD assessment test, *cNAT* COPD nocturnal symptom assessment test

**Fig. 3 Fig3:**
[figure not shown]
The study flow diagram. NIPPV, noninvasive positive pressure ventilation; COPD, chronic obstructive pulmonary disease; IOT, Internet of things; CHRF, chronic hypercapnic respiratory failure

The enrolled patients who are lost to follow-up, suffered serious adverse events, withdraw consent, or met endpoints will be regarded as a withdrawal. The Intervention and follow-up was terminated If one of the endpoints occurs: (1) death; (2) did not receive intervention as randomized; (3) the need for endotracheal intubation and invasive ventilation during exacerbation; (4) pneumothorax; (5) had active unstable coronary artery syndrome or cerebrovascular disease; (6) unable to tolerate noninvasive ventilation due to surgery and so on; and (7) cognitive impairment or unstable psychiatric morbidity.

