### Outcome and assessments

The primary study outcome was the SRI questionnaire, a 49-item questionnaire specifically designed for chronic respiratory failure patients with home mechanical ventilation. The domain scores are calculated by transforming the mean item score into a percentage ranging from 0 (worst quality of life) to 100 (best quality of life) [29, 30]. SRI questionnaire could not be an outcome but the score of SRI questionnaire.

Secondary outcomes were compliance with the ventilator, change in arterial PaCO2 and PaO2, change in lung function, time to readmission or death within 12 months from any cause, all-cause mortality, exacerbation and hospitalization frequency, safety analysis, cost-effectiveness analysis, and other health-related quality of life, measured by the modified Medical Research Council score (MRC) [31] to assess dyspnea (0 = no dyspnea, 4 = dyspnea at rest), the COPD assessment test (CAT) [32, 33], and COPD nocturnal symptom assessment test (cNAT).

Adherence with the ventilator was observed by monitoring the daily usage, usage days, ventilator settings, and other parameters in the IOT platform. Arterial blood gas analysis was taken during the daytime at rest without oxygen or ventilatory support unless patients were unable to stop ventilatory support even for short periods. Lung function was assessed according to national guidelines [28], including FEV1, FEV1% predicted, FVC, FVC % predicted, FEV1/FVC, total lung capacity, and residual volume. Hospital readmission and survival status of study patients were collected by checking medical records from the hospital or the general practitioner at each follow-up visit. For patients lost to clinical follow-up, each study center collected data from the national population register.

Occurrence time, severity, duration, adopted measure, and outcome of the adverse event occurring during the study should be recorded in the adverse events form according to the actual circumstances (Additional file 2). The common adverse events included facial rash, nasal ulceration, dry eyes, conjunctivitis, nasal stuffiness, nosebleed, gastric distension and device/mask intolerance [11, 17]. Serious adverse events were life-threatening, result in death, persistent, and significant disability, or incapacity, or make the participants’ hospitalization.

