The categorical variables will be compared by chi-square tests or Fisher’s exact tests as appropriate. We will use a general linear repeated measures analysis of variance with a Bonferroni correction or a paired t-test to analyze assessments changes within a group over time. The primary and appropriate secondary outcome analyses, such as compliance with the ventilator, change in arterial PaCO2 and lung function, will be performed including all randomized patients according to the intention-to-treat (ITT) principle. Missing data will be handled using the “last observation carried forward” method. We will use a linear mixed model to analyze the mean difference between the groups. When the conditions for use of the linear mixed model are not appropriate, a generalized estimating equation with correction for the baseline value and minimization variables (age, body mass index, frequency of COPD readmissions over 12 months) will be used. Time from randomization to death will be performed according to the ITT principle using the Kaplan–Meier approach and the log rank test. Hazard rate will be analyzed using a Cox proportional hazards regression model adjusted for minimization covariance. When the conditions for use of are not appropriate, the time-dependent cox regression model will be used. Safety analyses will be performed on all randomized patients. Additionally, per-protocol analyses of all outcomes will be analyzed as a sensitivity analysis, including patients finishing the study according to the protocol.

Two-sided P values less than 0.05 will be considered to be statistically significant. Statistical analyses will be performed using SPSS software (version 25.0, IBM SPSS).

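### Follow-up ends together with treatment after seven post-randomisation events, including non-receipt of the assigned intervention, which contradicts the intention-to-treat analysis; the serious-adverse-event withdrawal rule must also be reconciled

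*Protocol article*

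**What the plan says.** Two sentences after Fig. 3, in the protocol article's section Follow-up and endpoints, govern this point.

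- The first defines withdrawals: "The enrolled patients who are lost to follow-up, suffered serious adverse events, withdraw consent, or met endpoints will be regarded as a withdrawal".
- The second ends treatment and observation together: "The Intervention and follow-up was terminated If one of the endpoints occurs: (1) death; (2) did not receive intervention as randomized". The remaining events are "the need for endotracheal intubation and invasive ventilation during exacerbation", pneumothorax, unstable coronary or cerebrovascular disease, "unable to tolerate noninvasive ventilation due to surgery and so on", and cognitive or psychiatric illness.

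Outcome and assessments defines serious adverse events to include those that threaten life, "or make the participants’ hospitalization", with no limit by cause. The same section lists among the secondary outcomes "time to readmission or death within 12 months from any cause, all-cause mortality, exacerbation and hospitalization frequency". The main cost-effectiveness endpoint is cost per admission avoided.

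Sample size calculation and statistical analysis states that the primary and appropriate secondary analyses "will be performed including all randomized patients according to the intention-to-treat (ITT) principle". Time to death is also analysed by intention to treat. Missing values are filled by last observation carried forward (LOCF).

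**The concern.** Intention to treat needs outcomes from every randomised patient to month 12, whatever happened to treatment. Ending observation because a patient did not get the assigned intervention is the opposite of that. Several of the other terminating events mark a serious turn in the patient's course, so the missing outcomes are unlikely to resemble the observed ones. Loss can also differ by arm, because an intervention that changes use of the ventilator or the course of exacerbations can change who reaches a terminating event.

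At stake are the 12-month SRI score, gas exchange, compliance, readmissions and deaths after a terminating event. The sample size section frames the SRI comparison as non-inferiority with a margin of 5. In that setting, carrying forward scores from before a deterioration can make the arms look more alike than they are.

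The withdrawal sentence raises a second, conditional concern. Hospitalisation is both a serious adverse event and an outcome. If a withdrawal on that ground stops data collection, the outcome switches off its own measurement.

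**Working it through.** **1. The termination rule against the analysis rule.** Of the seven events, death properly ends observation. The other six can all occur in a patient who is alive and could still be assessed. The second event is a departure from allocation, which is exactly what intention to treat keeps in. The text names follow-up as well as intervention, so it cannot be read as covering treatment alone.

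**2. What is lost after a terminating event**, using the schedule in Table 1:

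- SRI and arterial blood gases are due at allocation and at months 3, 6 and 12. A patient terminated before month 3 has the baseline value carried to month 12; one terminated between months 6 and 12 has the month-6 value carried.
- Lung function is due only at allocation and month 12. Anyone terminated before month 12 gets the baseline value, that is, a change of zero.
- Readmission and survival are collected from medical records at each follow-up visit. Once visits end, so does this route.
- The population register is offered for patients lost to clinical follow-up. The withdrawal sentence lists that group separately from patients who met an endpoint, so it is unclear whether terminated patients are covered. A register cannot supply SRI, PaCO2 or compliance.

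The documents give no frequency for the seven events, so this part cannot be sized.

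**3. The serious-adverse-event rule, if withdrawal ends data collection.** The plan's own figure is a 25% loss: 200 × 0.25 = 50 patients, leaving 75 of 100 per arm. No 12-month hospitalisation rate is given. I assume that a share p of 30% to 70% is admitted at least once. Withdrawals on this ground alone are 200p. Patients left per arm are 100(1 − p), and the number per arm needed to keep 75 evaluable is 75/(1 − p).

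| p | Withdrawals of 200 | Left per arm | Per arm to keep 75 |
|---|---|---|---|
| 30% | 60 | 70 | 108 |
| 50% | 100 | 50 | 150 |
| 70% | 140 | 30 | 250 |

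The allowance is exceeded once p passes 25%.

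For hospitalisation frequency, assume Poisson admissions at rate λ per year, counted only up to the first. Then p = 1 − exp(−λ), so λ = −ln(1 − p), and the share of admissions missed is 1 − p/λ:

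- p = 30%: λ = 0.36, 16% missed.
- p = 50%: λ = 0.69, 28% missed.
- p = 70%: λ = 1.20, 42% missed.

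With an assumed true rate ratio of 0.70:

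- 0.5 against 0.35 per year is counted as 0.39 against 0.30 (ratio 0.75).
- 1.0 against 0.7 per year is counted as 0.63 against 0.50 (ratio 0.80; difference 0.13 instead of 0.30).

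These figures treat frequency as a count per patient. Dividing by observed time would recover the rate under this simple model, but not if admissions cluster within patients.

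**4. Scheduled admissions.** Follow-up and endpoints says that patients in both arms are admitted for the follow-up visits. The definition of a serious adverse event exempts no planned admission, so read literally it would make every patient who attends a withdrawal.

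The stated 100 per arm does not follow from its own inputs: 2 × (1.960 + 1.282)² × 20²/5² ≈ 336.3, so 337 evaluable per arm if the true difference is zero. That is a separate matter and nothing here rests on it.

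**The case against.** The strongest reply concerns hospitalisation. The withdrawal sentence does not say that follow-up stops; only the next sentence does, and neither serious adverse events nor hospitalisation is among its seven events. Had every admission ended follow-up, a separate entry for intubation during an exacerbation would be largely redundant. Table 1 schedules readmission and exacerbation through month 12, hospitalisation frequency is an outcome, and the cost analysis covers all readmissions. A rule that would withdraw patients for attending scheduled visits is unlikely to be intended. This reply stands. A reader might infer that hospitalisation frequency cannot exceed one, but the documents do not establish that.

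A reader might also infer that the intention-to-treat analysis shrinks to patients who stayed well and adherent. It does not: LOCF keeps withdrawn patients in the analysis, and the analysis of those who finish according to protocol is a separate sensitivity analysis. The defect lies in the values carried forward.

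Three further limits are fair:

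- The outcome "time to readmission or death within 12 months from any cause" is already complete when the first readmission is the triggering event. Only terminating events that are not themselves readmissions or deaths can cut it short.
- The register may recover deaths, so mortality may be incomplete rather than certainly truncated.
- The intolerance item is tied to surgery and similar causes. It should not be read as all mask or device intolerance, which the article lists among common adverse events. Nor is every terminating event evidently one that the intervention would change.

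None of this answers the explicit end of follow-up for the seven events, or its conflict with intention to treat over non-receipt of the assigned intervention.

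**Conclusion.** The contradiction holds and needs no assumption: the article ends follow-up for seven post-randomisation events, one of them a departure from allocation, and promises intention-to-treat analysis of everyone randomised. Its effect on SRI, gas exchange, compliance, later readmissions and later deaths is real but cannot be sized from the documents, and the direction of bias is not known in advance.

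The serious-adverse-event rule is an ambiguity to resolve, not a demonstrated truncation. The 60 to 140 withdrawals against 50, and the 16% to 42% of admissions missed, hold only if withdrawal on that ground ends data collection, if 30% to 70% of patients are admitted within the year and, for the undercount, if admissions follow a Poisson process and are counted per patient.

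This should be corrected, because outcomes that were never collected cannot be restored at analysis.

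**What to change.** Leave decisions on stopping treatment as they are and separate them from data collection.

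- State that only death or withdrawal of consent to data collection ends follow-up, and that neither a serious adverse event nor non-receipt of the assigned intervention is a ground for ending it.
- Keep the month 3, 6 and 12 SRI, readmission and vital-status assessments, where feasible, for all other patients.
- Extend the medical-record and register checks to every randomised patient, including those already terminated.
- Reconcile Follow-up and endpoints, Outcome and assessments, and the statistical section on the withdrawal rule. Say what withdrawal means for data collection after a serious adverse event, and whether the scheduled follow-up admissions count as hospitalisations.

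The cost is an amendment and continued visits for patients who would have been dropped; the visits and record checks are already scheduled. The gain depends on timing. Trial status gives recruitment from January 2019 to January 2022, so with 12 months of follow-up the last visits would fall around January 2023. Readmissions and deaths may still be traced retrospectively, but SRI visits already missed cannot be recovered. The report should give their number by arm and by terminating event.
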